### Interim analyses {21b}

Interim analysis will be performed. When we complete the enrollment of 60 patients, 30 of whom are in the ketorolac group and 30 in the placebo group, we will perform an interim analysis.

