## Statistical methods

### Statistical methods for primary and secondary outcomes {20a}

Statistical analysis will be performed using SPSS software (version 26.0) and R (× 64 3.5.0). Continuous variables will be presented as mean ± standard deviation. The Kolmogorov–Smirnov test will assess normal distribution. If variables exhibit normal distribution, an independent sample *t*-test will be employed; otherwise, the Mann–Whitney *U* test will be utilized. Categorical variables’ frequency will be expressed as percentages and analyzed using the chi-square test or Fisher’s exact test. It should be noted that we are not conducting an Intention to Treat analysis due to the exclusion of patients with more than 10% missing data. Double-tailed *p*-values and 95% confidence intervals will be reported, with statistical significance defined as *p* < 0.05.

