### Composition of the data monitoring committee, its role and reporting structure {21a}

The Data and Safety Monitoring Board (DSMB) is composed of a chair, who is a cardiologist, along with a cardiac surgeon, an independent statistician, a cardiac anesthesiologist with expertise in medical ethics and law, and a clinical pharmacologist. The DSMB will formulate tailored data security monitoring plans, taking into consideration the magnitude of associated risks. Given the high-risk nature of this study, an autonomous Data Security Monitoring Committee has been established to systematically oversee the accumulated data on security and effectiveness. The committee’s mandate is to provide well-informed recommendations regarding the continuation of the research.

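### The interim at 60 of 120 patients has no stated purpose or boundary and the only threshold is p < 0.05; if efficacy is tested by chi-square at both looks, type I error is about 8%

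*Protocol article*

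**What the plan says.** Four places in the protocol article bear on this.

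- **Interim analyses {21b}**: "Interim analysis will be performed". The trigger is "When we complete the enrollment of 60 patients, 30 of whom are in the ketorolac group and 30 in the placebo group". The section names no endpoint, test, threshold, purpose or consequence.
- **Statistical methods for primary and secondary outcomes {20a}**: "Double-tailed *p*-values and 95% confidence intervals will be reported", "with statistical significance defined as *p* < 0.05". This is the only significance level in the document. Categorical outcomes are to be "analyzed using the chi-square test or Fisher’s exact test".
- **Sample size {14}**: event rates of 70% and 40%, 53 per arm, raised to 60 per arm for losses to follow-up. Nothing is allowed for an interim look.
- **Composition of the data monitoring committee {21a}**: a committee is set up "to systematically oversee the accumulated data on security and effectiveness" and recommends on whether the research continues.

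The Trial design section calls the trial a superiority test. Trial status reports 55 patients included on 20 March 2024, five short of the trigger.

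**The concern.** The article fixes the timing of a second look, one unadjusted threshold and a single-look sample size, and it does not say how they fit together. A team following the text has only p < 0.05 to apply at 60 patients and again at 120. If efficacy is tested each time, a false-positive result has two chances to occur, and neither the 5% error rate nor the 95% confidence interval has its stated meaning.

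The estimate is also at stake. A result declared on 30 per arm because it crossed p < 0.05 tends to overstate the effect. Timing adds to this, because a boundary chosen after the interim data are seen does not protect the error rate.

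**Working it through.** **Inputs.** From the protocol: two-sided 0.05; chi-square or Fisher's exact test; looks at 30 and 60 per arm; 53 evaluable per arm after losses; event rates 70% and 40%. Assumed for the calculation: the efficacy composite is tested at both looks and success can be claimed at either.

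**1. The plan's own figure.** The Sample size section states no significance level. I take two-sided 0.05 from the statistical methods and read its 90% confidence as power. With unpooled variance:

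n = (1.960 + 1.282)² × (0.7×0.3 + 0.4×0.6) / 0.30² = 10.51 × 0.45 / 0.09 = 52.5, so 53 per arm.

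Allowing 10% loss, 53 / 0.9 = 58.9, so 59, rounded to 60. The figure is reproduced as a fixed design with one test at 0.05.

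**2. Two looks, normal theory.** Under the null the two test statistics are bivariate normal with correlation √t, where t is the information fraction. The overall error is 1 − P(|Z₁| < 1.96 and |Z₂| < 1.96).

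| t | Type I error |
|---|---|
| 0.4 | 8.63% |
| 0.5 | 8.31% |
| 30/53 = 0.566 | 8.08% |
| 0.6 | 7.96% |

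**3. Two looks, exact.** All binomial outcomes at 30 per arm are enumerated. Those that do not reject are carried on to the final look and tested again at 0.05.

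| Test at both looks | Null rate | 60 per arm at end | 53 per arm at end |
|---|---|---|---|
| Chi-square, uncorrected | 0.40 | 8.30% | 8.18% |
| | 0.55 | 8.67% | 7.92% |
| | 0.70 | 8.43% | 8.18% |
| Fisher's exact | 0.40 | 4.95% | 4.91% |
| | 0.55 | 5.22% | 4.72% |
| | 0.70 | 4.87% | 4.67% |

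For reference, one final chi-square test at 60 per arm has an error of 5.1–5.4%, and one final Fisher test 3.1–3.4%. The second look therefore adds error under either test; Fisher's conservatism absorbs it.

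**4. What an unadjusted efficacy look would show.** Under 70% v 40%, chi-square at 30 per arm gives p < 0.05 with probability 66%, and the mean observed difference in those trials is 37 points against a true 30. Under 55% v 40% (an assumed smaller effect), the probability is 22% and the mean is 32 points against a true 15.

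**5. Limits that hold the error.** Solving for an overall two-sided 0.05 at t = 0.5, O'Brien-Fleming gives z = 2.797 and 1.977, that is p < 0.0052 at the interim and p < 0.0480 at the end. Power under 70% v 40%, by exact chi-square enumeration:

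| Final n per arm | Single look at 0.05 | O'Brien-Fleming, two looks |
|---|---|---|
| 60 | 92.4% | 92.5% |
| 53 | 87.8% | 87.4% |

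Because the data are discrete, these limits give an exact error of 5.0–5.6% at 60 per arm, close to the 5.1–5.4% of a single chi-square test.

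**The case against.** A reader might infer that p < 0.05 governs every analysis, including the interim, and that an early stop for efficacy is therefore likely. The document does not support that. The threshold stands under the methods for primary and secondary outcomes. The interim section names no test, and no stopping rule or right to claim success at 60 patients appears anywhere. The 66% crossing probability is thus an illustration of an unadjusted look, not a forecast for this trial.

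A harmless reading is also open. The Outcomes section lists safety events as part of the primary endpoint, and a committee can review effectiveness and advise on continuation without any early efficacy claim. A look for safety or futility only would not inflate the type I error. Boundaries often sit in an analysis plan or committee charter, neither of which is shown, and the article says that the committee will draw up monitoring plans.

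The size depends on the test as well. Fisher's exact test is permitted and would keep the error near 5%.

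All of this stands and makes the point conditional. It does not remove it. The article itself prints the second look, the single threshold and the single-look sample size, and gives the committee effectiveness data, so the text as written leaves 0.05 as the only rule at both looks. At event rates of 40–70%, chi-square is the likelier test. If a boundary exists elsewhere, stating it here costs a sentence.

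**Conclusion.** The point holds in conditional form. The interim has no stated purpose or boundary, and the only printed threshold is unadjusted. If the efficacy composite is tested by uncorrected chi-square at two-sided 0.05 at both looks, with success claimable at either, the type I error is about 8% instead of about 5%: 8.3–8.7% if all 60 per arm are analysed at the end, 7.9–8.2% with the planned 53. With Fisher's exact test at both looks it is 4.7–5.2%. With a safety-only look, or no early efficacy claim, there is no inflation. The documents do not show which case applies, and that is what needs settling before the interim.

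**What to change.** Before any interim data are seen, state one of two rules in the interim and statistical methods sections:

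- **(a)** No efficacy claim is made at the interim, and the final test stays at two-sided 0.05.
- **(b)** Efficacy is tested at O'Brien-Fleming limits, p < 0.0052 at the interim and p < 0.0480 at the end. Use Lan-DeMets spending if the information fraction is not 0.5. It may well differ, because the trigger is enrolment of 60 while follow-up runs to 90 days, and because fewer than 60 per arm may be evaluable at the end.

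If the analysis plan or committee charter already holds a boundary, copy it here.

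The cost is a sentence or two and no added patients. Rule (a) costs no power. Rule (b) costs under half a point: 92.5% v 92.4% for a single look at 60 per arm, 87.4% v 87.8% at 53. The 53-per-arm figures fall below the planned 90% with or without the interim, because exact chi-square power is lower than the unpooled approximation used for sizing. The downside of (b) is that a moderate interim p-value, such as 0.02, no longer counts as significant.

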### Methods for additional analyses (e.g., subgroup analyses) {20b}

There are no subgroup analyses planned.

### Methods in analysis to handle protocol non-adherence and any statistical methods to handle missing data {20c}

We allow patients to have 10% missing data, which will be deleted as blank. When the patient’s data is missing by more than 10%, the patient will be deleted.

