### Intervention description {11a}

The surgeries will be performed by [name]. The study will commence on the day the patients sign an informed consent form and receive their randomized numbers. The ketorolac group, consisting of patients with aTAAD, will be treated with ketorolac. They will receive a preoperative intramuscular injection of 60 mg per 2 ml ketorolac and a postoperative injection of 30 mg per 1 ml ketorolac BID for two consecutive days. The placebo group, also consisting of patients with aTAAD, will receive placebo treatment. They will receive a preoperative intramuscular injection of 2 ml 0.9% saline placebo and a postoperative injection of 1 ml 0.9% saline placebo BID for two consecutive days. During the administration of ketorolac, patients’ blood pressure and renal function will be routinely monitored, and targeted treatment methods such as sedation, hypotension, diuresis, and dialysis will be applied as necessary. Additionally, all included patients will receive the same medical and surgical treatments in accordance with the diagnosis and treatment guidelines for aTAAD. Aortic dissection tissue samples will be collected for laboratory study during the surgery. Both the ketorolac group and the placebo group patients will undergo follow-up examinations before surgery and on the 1st, 3rd, 5th, 7th, 30th, and 90th day after surgery. These examinations will include assessments of adverse drug events, cardiac ultrasound, chest X-ray, laboratory tests (blood routine examination, blood biochemistry, erythrocyte sedimentation rate, coagulation function, CK-MB, cardiac troponin I (cTnI), PCT, IL-6, CRP, myohemoglobin (MYO), type B natriuretic peptide (BNP), D-dimer, etc.) and clinical biomarkers (matrix metalloproteinase-9 (MMP-9), MMP-2, MMP-3, MMP-13, type III procollagen, etc.). CTA examination of the cervical, thoracic, and abdominal aorta artery will be performed before surgery and on the 30th and 90th days after surgery.

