### Outcomes {12}

#### Primary endpoint

Efficacy: death, organ malperfusion syndrome, permanent dialysis, tracheotomy, neurological impairment, postoperative mechanical circulatory support, and unplanned cardiac reoperation.

Safety: gastrointestinal ulceration, gastrointestinal bleeding, gastrointestinal perforation, postoperative hemorrhage (postoperative hemorrhage exceeding 1000 ml within 24 h), renal failure, liver failure, drug allergies, and other severe adverse events following drug administration.

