### Sample size {14}

The required sample size was calculated using the PASS (15.0.5) software. The primary endpoint of efficacy was used to calculate the sample size. In the literature, the total death rate of hospitalization after surgery was 25% [7], the incidence of organ malperfusion syndrome was 15–33% [19, 20], permanent dialysis was 2.6% [21], tracheotomy was 8% [22], neurological impairment was 6.9% [22], postoperative mechanical circulatory support was 20% [23], unplanned cardiac reoperation was 4.2% [24], and postoperative cardiac arrest was 0.7–5.2% [25]. Therefore, we assumed that the incidence of composite endpoint events in the control group is 70%, and the incidence of composite endpoint events in the ketorolac group is reduced to 40%. Using PASS (15.0.5) software, when the sample size of the ketorolac group and the control group is 53 cases, this difference can be detected with over 90% confidence. Considering that the loss of follow-up rate is higher than 10%, the final total sample size of this experiment is 120 cases, with 60 cases in the experimental group and 60 cases in the control group.

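### Patients with more than 10% missing data are deleted, with no exception for death or an observed primary event, so the primary comparison depends on what happens after randomisation

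*Protocol article*

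**What the plan says.** All references are to the Protocol article.

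- Section {20c} (non-adherence and missing data) has two rules. Up to the threshold, gaps stay blank: "We allow patients to have 10% missing data, which will be deleted as blank". Above it, the whole patient goes: "When the patient’s data is missing by more than 10%, the patient will be deleted".
- Section {20a} (statistical methods) draws the consequence for the analysis population: "we are not conducting an Intention to Treat analysis due to the exclusion of patients with more than 10% missing data".
- Outcomes {12} defines the primary efficacy endpoint: "Efficacy: death, organ malperfusion syndrome, permanent dialysis, tracheotomy, neurological impairment, postoperative mechanical circulatory support, and unplanned cardiac reoperation".
- Intervention description {11a} schedules "follow-up examinations before surgery and on the 1st, 3rd, 5th, 7th, 30th, and 90th day after surgery". Table 1 adds an intraoperative time point, giving eight in all.
- Sample size {14} takes in-hospital death after surgery as 25% and the composite as 70% on placebo and 40% on ketorolac.
- Procedure for unblinding {17b} counts patients unblinded in an emergency as withdrawals.

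No section exempts patients who die or who already have a primary event. None says what the 10% is a percentage of, or whether assessments due after death are missing.

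**The concern.** Whether a patient is analysed depends on the completeness of that patient's record, which is settled after randomisation and is tied to the outcome. A patient who dies cannot attend later visits, and a very ill patient is more likely to miss them. The rule removes the whole patient rather than the affected variable, so a known primary event can be discarded because unrelated laboratory or imaging results are absent.

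At stake is the randomised comparison itself. If deaths are deleted, the primary analysis compares survivors with near-complete data. Ketorolac may affect survival, so those survivors need not be comparable between arms.

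**Working it through.** **1. The plan's own figure.** Two proportions, two-sided alpha 0.05, 90% power, unpooled variance: (1.960 + 1.282)² × (0.7×0.3 + 0.4×0.6) / 0.3² = 52.5, so 53 per arm, as stated. The increase to 60 per arm allows for 7 losses (7/60 = 11.7%).

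**2. How much a death leaves missing.** Table 1 has 45 assessment cells: vital signs 8, hematology 8, CTA 3, chest X-ray 6, echocardiography 4, adverse events 8, complications 8. If cells due after death count as missing:

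| Time of death | Cells lost | Share of 45 |
|---|---|---|
| Before day 1 | 35 | 78% |
| Day 1 to before day 3 | 30 | 67% |
| Day 3 to before day 5 | 24 | 53% |
| Day 5 to before day 7 | 19 | 42% |
| Between days 7 and 30 | 14 | 31% |
| Between days 30 and 90 | 7 | 15.6% |

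Counting visits instead, a death after day 30 loses 1 of 8 (12.5%), or 1 of 7 (14.3%) without the intraoperative point. On both counts every death before day 90 exceeds 10%.

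Counting single data items needs assumptions. I took 10–30 laboratory items per visit, 0 or 12 ELISA analytes at the five sampling times, and 0–50 one-off items. A death before day 30 then loses 14–27%, and a death between days 30 and 90 loses 7–14%, on either side of the threshold.

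**3. Survivors.** The same counts apply to a survivor who misses visits and whose gaps are not filled from elsewhere. Missing both the day-30 and day-90 visits exceeds 10% on every count above. Missing day 90 alone is 15.6% of cells but 7–14% of items.

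**4. Effect on the placebo arm.** Expected events: 0.70 × 60 = 42. Expected deaths, all of them events: 0.25 × 60 = 15. With the deaths deleted, 27 events remain among 45 patients (60%), and 15/42 = 36% of expected events are lost. Fifteen deletions is about twice the allowance of 7.

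**5. Effect on the contrast.** The rate left after deleting deaths is (composite − death) / (1 − death). Power uses the pooled Z test: Φ[(|p1 − p2| − 1.96·SE0)/SE1], where SE0 uses the pooled rate and SE1 the two separate rates. With nobody deleted, 70% vs 40% at 60 per arm gives 92%. Below, placebo deaths are 25% and the true composite stays at 70% vs 40%. The ketorolac death rates are my assumptions, because the protocol gives none.

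| Ketorolac deaths | Analysed n (placebo, ketorolac) | Analysed rates | Difference (true 30 points) | Power |
|---|---|---|---|---|
| 10% | 45, 54 | 60% vs 33.3% | 26.7 | 76% |
| 14.3% | 45, 51.4 | 60% vs 30% | 30 | 85% |
| 20% | 45, 48 | 60% vs 25% | 35 | 94% |
| 25% | 45, 45 | 60% vs 20% | 40 | 98% |
| 35% | 45, 39 | 60% vs 7.7% | 52.3 | over 99% |

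The 14.3% row gives deaths the same share of the composite as on placebo (0.40 × 25/70). Below that rate the benefit is understated; above it, overstated. The more ketorolac deaths are deleted, the better ketorolac looks.

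**6. A harm example.** Assume deaths of 25% vs 40% and a 60% non-fatal event rate among survivors in both arms. The true composites are 0.25 + 0.75×0.6 = 70% and 0.40 + 0.60×0.6 = 76%. After deletion both are 60%. This shows bias in the estimate, not a detectable signal being hidden: the full analysis would have only about 11% power for 70% vs 76%.

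**The case against.** The strongest objection is that {20c} does not say assessments due after death are missing. If each patient's data are counted only up to death, few deaths need be removed. A reader might infer that the rule as written removes nearly every death. The text neither says nor excludes this, so the point must stay conditional. The gap does not rescue the plan, because it leaves the inclusion of deaths to a choice that is not fixed in advance.

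A reader might also infer that one missed visit deletes a patient. That is not established: the rule speaks of the patient's data, visits carry unequal amounts, and on an item count the day-90 visit may fall below 10%. Hospital records, telephone prompts and an end-of-follow-up interview may also fill gaps.

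A third tempting reading is that the harm is a loss of power. The table in the working shows power falling or rising with an unknown ketorolac death rate.

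Finally, a mortality harm would not disappear from the trial. Death is a listed safety variable, serious adverse events are reported, and the DSMB reviews accumulating safety and effectiveness data. This stands, but those routes do not repair the primary comparison.

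A separate analysis plan may exist, but these two sections state the rule and reject ITT outright, so this is not a detail left open.

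**Conclusion.** The concern holds in conditional form and should be fixed before the primary analysis. What is certain is that the protocol rejects ITT and deletes whole patients on an undefined completeness threshold, with no protection for deaths or observed events. If assessments due after death count as missing, the rule can delete most or all deaths, and the expected placebo rate falls from 70% to 60%. If they do not, randomised survivors with known composite status can still be deleted for missed visits.

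The harm is bias of unknown direction. For assumed ketorolac death rates of 10% to 35%, a true 70% vs 40% is analysed as anything from 60% vs 33% to 60% vs 8%. These figures rest on the plan's 25%, 70% and 40%, on deletion of deaths only, and on the ketorolac composite being held at 40%. The sample size of 53 per arm reproduces and is not in question here.

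**What to change.** Rewrite {20a} and {20c} so that:

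- the primary analysis includes all randomised patients in the arm allocated;
- any observed component, death included, counts as an event whatever else is missing;
- the status of survivors with missed visits is taken from the electronic medical record and the telephone interview already planned in {18a};
- patients whose status remains unknown are handled by a prespecified method, with a worst-case sensitivity analysis;
- the 10% deletion set is kept, if at all, only as a labelled sensitivity analysis, with its denominator defined.

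Apply the same to {17b}: patients counted as withdrawals after emergency unblinding stay in the primary analysis in their allocated arm.

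The cost is an amendment with ethics notification and a registry update under {25}, plus a little more analysis work. Status for most patients should come from sources already planned, although follow-up of patients counted as withdrawals needs to be confirmed. The change is best made before the interim analysis at 60 patients; the Trial status section reports 55 already included on 20 March 2024.

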### Plans to give access to the full protocol, participant-level data, and statistical code {31c}

The datasets used and/or analyzed during the current study can be made available by the corresponding author upon reasonable request.

## Oversight and monitoring

### Composition of the coordinating center and trial steering committee {5d}

This study is a single-center study conducted at Nanjing Drum Tower Hospital. The trial involves various roles:

Principle investigator: oversees the trial and has medical responsibility for the patients.Data manager: organizes data capture and ensures data quality.Study coordinator: handles trial registration, coordinates study visits, and prepares annual safety reports.Study physician: obtains informed consent, and ensures follow-up according to the protocol.A research assistant: randomizes the patients and administers the drug.Statistician: creates random scales and provides consultation on statistical methods.The study team holds weekly meetings. There is no trial steering committee or stakeholder and public involvement group.

### Composition of the data monitoring committee, its role and reporting structure {21a}

The Data and Safety Monitoring Board (DSMB) is composed of a chair, who is a cardiologist, along with a cardiac surgeon, an independent statistician, a cardiac anesthesiologist with expertise in medical ethics and law, and a clinical pharmacologist. The DSMB will formulate tailored data security monitoring plans, taking into consideration the magnitude of associated risks. Given the high-risk nature of this study, an autonomous Data Security Monitoring Committee has been established to systematically oversee the accumulated data on security and effectiveness. The committee’s mandate is to provide well-informed recommendations regarding the continuation of the research.

